## Abstract

**Background:**

Trauma contributes to psychosis and in psychotic disorders post-traumatic stress disorder (PTSD) is often a comorbid disorder. A problem is that PTSD is underdiagnosed and undertreated in people with psychotic disorders. This study’s primary goal is to examine the efficacy and safety of prolonged exposure and eye movement desensitization and reprocessing (EMDR) for PTSD in patients with both psychotic disorders and PTSD, as compared to a waiting list. Secondly, the effects of both treatments are determined on (a) symptoms of psychosis, in particular verbal hallucinations, (b) depression and social performance, and (c) economic costs. Thirdly, goals concern links between trauma exposure and psychotic symptomatology and the prevalence of exposure to traumatic events, and of PTSD. Fourthly predictors, moderators, and mediators for treatment success will be explored. These include cognitions and experiences concerning treatment harm, credibility and burden in both participants and therapists.

**Methods/Design:**

A short PTSD-screener assesses the possible presence of PTSD in adult patients (21- to 65- years old) with psychotic disorders, while the Clinician Administered PTSD Scale interview will be used for the diagnosis of current PTSD. The M.I.N.I. Plus interview will be used for diagnosing lifetime psychotic disorders and mood disorders with psychotic features. The purpose is to include consenting participants (N = 240) in a multi-site single blind randomized clinical trial. Patients will be allocated to one of three treatment conditions (N = 80 each): prolonged exposure or EMDR (both consisting of eight weekly sessions of 90 minutes each) or a six-month waiting list. All participants are subjected to blind assessments at pre-treatment, twomonths post treatment, and six monthspost treatment. In addition, participants in the experimental conditions will have assessments at mid treatment and at 12 months follow-up.

**Discussion:**

The results from the post treatment measurement can be considered strong empirical indicators of the safety and effectiveness of prolonged exposure and EMDR. The six-month and twelve-month follow-up data have the potential of reliably providing documentation of the long-term effects of both treatments on the various outcome variables. Data from pre-treatment and midtreatment can be used to reveal possible pathways of change.

**Trial registration:**

Trial registration:
ISRCTN79584912

## Background

### Links between trauma, PTSD and psychosis

Of patients who have ever experienced psychotic episodes, 50% to 98% report having been exposed to one or more traumatic events in their lives [1]. As a result, the prevalence of post traumatic stress disorder (PTSD) in people with psychotic disorders ranges from 12% to 29% [2,3]. This can be considered high compared to estimated prevalence rates in the general population, which range from 0.4% to 3.5% [4-6].

In a meta-analytical study evidence was found that major adversities in childhood (before the 18th year of life) increase the risk of psychosis by 2.8 times on average [7]. A dose–response relationship was found in almost all studies: the more severe the trauma, the greater the risk of developing psychosis. Childhood trauma as a major risk factor probably adds 33% to the onset of psychosis in society [7]. Significant associations between all types of childhood adversities (except the loss of a parent) and symptoms of paranoia and auditory hallucinations have been reported [7,8]. Childhood sexual abuse is associated with hallucinations (odds ratio (OR) 8.9, confidence interval (CI) = 1.86 to 42.44), and being brought up in institutional care is specifically associated with paranoia (OR = 11.08, CI = 3.26 to 37.62 [8].

Traumatic events, PTSD and psychosis appear to have several interactions. The presence of a comorbid PTSD has been found to have a negative impact on the course and prognosis of the psychotic disorder [9], and the combination of psychosis and PTSD appears to be associated with poorer social functioning and greater risk of relapsing in psychosis [9-11]. There are also indications that the content of hallucinations may fully match that of experienced traumas (12.5%) or the themes of hallucinations can be very similar to that of experienced traumas (45%) [12]. The occurrence of re-experiencing symptoms of PTSD is strongly associated with a predisposition to hallucinations. Negative beliefs about self and others have been found to be associated with a predisposition to paranoia [13].

There is also evidence to suggest that experiencing a psychotic episode, and experiencing problems with the health care system, may potentially be experienced as traumatic events and may result in PTSD [13-15].

Considering these findings and being aware that PTSD in general is associated with forms of non-effective coping, more abuse of alcohol and drugs, negative self-esteem, negative expectations of other people, and a greater risk of exposure to future potentially traumatic events [16], it becomes clear that trauma exposure is associated with impairment and major health problems in patients with psychosis, creating a burden for both patients and society [17,18].

### Clinical attitudes and practice

In clinical practice, trauma exposure, PTSD and their links to psychosis do not seem to get that much attention. Traumatic experiences and the diagnosis of PTSD appear to be underreported in the charts of patients with a severe mental illness or psychotic disorder [19,20]. In addition, clinicians are reluctant to address trauma histories in patients with psychosis [21,22]. They will not easily offer therapy, especially not exposure therapy, to overcome PTSD symptoms; instead, they suggest establishing trust and rapport with patients first, and giving patients a sense of mastery, before starting to explore traumatic experiences the patients might have had [23]. Many clinicians seem to fear that trauma treatment with this patient group will lead to symptom exacerbation, crisis, hospitalization, self-harm and suicidal behavior, or rapid changes in medication. They presume that before a PTSD treatment can be safely conducted, stabilizing interventions are necessary [23,24].

### Studies examining PTSD treatment efficacy

Meta-analytic studies of clinical trials show that, generally speaking, trauma focused cognitive behavioral therapy (TF-CBT), such as prolonged exposure (PE), and eye movement desensitization and reprocessing (EMDR) are safe and effective. These treatments should be the first-line psychological treatment for PTSD [25-27]. Unfortunately, people with a psychotic disorder are often excluded from PTSD treatment efficacy research [28,29]. Therefore, not much is known about the generalizability of PE or EMDR efficacy to people with psychotic disorders [30]. This question of applicability of PE and EMDR in patients with psychosis is the starting point of the present study protocol.

A number of studies have already addressed this issue. In a randomized controlled trial (RCT), the effects of Cognitive Behavior Therapy (CBT) were investigated in 108 participants with severe mental illness, of which 14% (N =17) had a diagnosis of schizophrenic or schizoaffective disorder [31]. The protocol consisted of 12 to 16 sessions of combined CBT interventions (a crisis plan, psycho-education, breathing exercise, cognitive restructuring). CBT proved to be effective in reducing PTSD symptoms and was safe. In an open study, the effect of PE in people with psychosis was studied [32]. Participants (N = 20) were given fourteen preparatory sessions and eight PE sessions. The drop out was high during preparatory sessions and this phase did not result in a decline of symptoms. A high compliance, no adverse events and a significant reduction of PTSD symptoms, during and after PE, were, however, noted. These results suggest that PE is effective and safe and preparation for PE may be unnecessary.

Recently, our research group conducted two small feasibility trials. The first, an open study (N = 27), used EMDR for PTSD in people with a life time history of psychosis [33]. The second study used EMDR (N = 5) and PE (N = 5) in a multiple baseline controlled design [34]. Results showed that both treatments were effective in reducing PTSD symptoms. [name] and [name] [33] found significant reductions in end-state PTSD, symptom severity of PTSD, delusions, hallucinations, depression and anxiety and an increase in self-esteem. [name] and colleagues [34] found significant reductions of PTSD and of general psychopathology and distress. In both studies no serious adverse events or symptom exacerbations were found. Both treatments were well accepted by participants and attrition was low. Taken together, results from pilot studies suggest that trauma-focused treatments, such as PE and EMDR, can be effectively and safely applied to patients with psychotic disorders, but well-controlled studies are lacking. To fill this gap, we set up the present study, the Treating Trauma in Psychosis (T.TIP) study.

## Objectives

### Primary objective –effects of treatment on PTSD symptoms and safety

In a sample of patients who receive treatment as usual (TAU) for a current diagnosis of psychosis this study examines: a) the efficacy of PE versus waiting list, and of EMDR versus waiting list, on the symptomatology of a comorbid PTSD; and b) the safety of PE versus waiting list and EMDR versus waiting list in the treatment of PTSD.

### Secondary objectives - effects of treatment on psychopathology and cost effectiveness

Other objectives were to determine the efficacy of PE versus waiting list and of EMDR versus waiting list on the symptomatology of psychosis. In this context the experience sampling method (ESM) [35] will be applied to examine the effects of treatment on temporal associations between intrusions, daily events and activities, and verbal hallucinations, depression,social functioning andpost traumatic cognitions.An economic evaluation will determine the cost effectiveness of the PTSD treatments.

### Tertiary objectives - links between trauma exposure, PTSD and psychosis

An important objective is to assess, in the psychosis sample, exposure to traumatic events, to assess and calculate the risk of having a comorbid PTSD, and to diagnose comorbid PTSD. In this context, the diagnostic accuracy of the Trauma Screening Questionnaire [36], in the population of patients with psychotic disorder, will be examined.

The present T.TIP study will address the question as to whether certain types and severities of trauma exposure are associated with specific phenomenological aspects of psychotic symptoms [7,8,37,38]. Specifically, the study aims to explore the links between traumatic events, PTSD and verbal hallucinations [12,33].

### Quaternary objectives – mediators, moderators and predictors of treatment outcome

In the intervention study we will conduct additional research to explore mechanisms of changes in the treatment outcome variables. Variables that are potential predictors, mediators and moderators will be examined, such as: a) bullying [7,8]; b) tonic immobility [39-41]; c) the capacity of participants’ working memory [42,43]; d) credibility of treatment and burden of treatment [44,45]. Both participants and therapists will have cognitions about treatment that may affect treatment outcome. Therefore assessments will be made of harm expectancy and harm experience, expected burden and experienced burden and credibility of treatment; e) demographic and trauma characteristics; f) self esteem [46-48]; g) personal beliefs about illness [49,50]; h) post traumatic cognitions [51]; i) cognitive biases [52-54]; j) cognitions about voices; k) memory characteristics [55-58]; and l) social support during treatment [59,60].

## Methods/Design

### Design

The T.TIP study is a single blind randomized controlled trial with three arms: PE, EMDR and a waiting list. The three groups are compared at pre-treatment (T0), at post treatment at two months (T2) and at six months (T6), on a set of variables that are linked to the various research questions. Mediator and moderator variables are assessed again at midtreatment (T1). A 12-month treatment intervention follow-up measurement (T12) will give indications whether treatment effects endure. The waiting list condition will receive the treatment of choice after sixmonths (T6).

The assessing research assistants are blind to the participants’ research condition.

The design of this study was approved by the Medical Ethics Committee of the medical centre of the VU University and is registered as N:36649.029.12.

### Participants

Patients, 18- to 65-years old, with a chart diagnosis of psychotic disorder or a mood disorder with psychotic features according to the Diagnostic and Statistical Manual of Mental Disorders, fourth edition text revsion(DSM-IV-TR) are recruited from outpatient services of thirteen mental health organizations in the Netherlands. The trial process starts with a short self-report screening. During the screening, participants report on traumatic events that fulfill DSM-IV-TR PTSD criterion A1 and associated PTSD symptoms using the 10 item Trauma Screening Questionnaire (TSQ) [36]. If participants report traumatic events and score above the TSQ’s cut-off criterion (*x* = ≥6), and give informed consent for further interviewing, an appointment will be made for the inclusion interview.

### Inclusion and exclusion

The criteria for inclusion in the intervention study are: a) age between 18 and 65 years; b) a lifetime history of a psychotic disorder or a mood disorder with psychotic features (M.I.N.I. plus); c) meeting DSM-IV-TR diagnostic criteria for PTSD (Clinician Administered PTSD Scale (CAPS)).

The criteria for exclusion are: a) high suicidality, operationalized as the combination of having a high suicidality score on the M.I.N.I. with the last suicide attempt within the past six months and a depression score on the Beck Depression Inventory-II (BDI-II) of 35 or higher; b) changes in medication (mood regulators, antipsychotics) within two months prior to the study; c) insufficient competence in the Dutch language; d) severe intellectual impairment, defined as an estimated IQ below 70 (mental retardation); e) not being able to travel to and from the place of assessment and therapy; and f) participant is in seclusion or admitted to a closed ward.

See Figure 1, the T.TIP flowchart. All mental health teams that signed up for cooperation in the T.TIP study carry out the standard procedure for screening of all patients suffering from psychosis. After that, the flow of consenting and screened participants into the study has three pathways: (1) ‘regular’ inclusion, meaning that each patient demonstrating a high risk for PTSD (TSQ ≥6) will be invited for an inclusion interview; (2) ‘low TSQ’ inclusion, meaning that a random sample of patients across the teams (N = 200) demonstrating a low risk of having a PTSD (TSQ ≤5) will be invited for a ‘low TSQ’-inclusion interview; and (3) ‘incidental referrals’-inclusion.

The inclusion interview conducted by the research assistant (RA) will be the same for all three categories ‘regular’, ‘low TSQ’ and ‘incidental referrals’: (a) three sections of the M.I.N.I.-Plus interview for assessing psychotic disorders, mood disorders with psychotic features and a risk analysis regarding acute suicidality; (b) the CAPS [61] for assessing a PTSD diagnosis; and (c) the BDI-II [62] for assessing the severity of depressive symptoms.

‘Regular’ participants who meet the inclusion criteria and give consent go to the randomization phase. ‘Low TSQ’-participants who appear to meet all criteria for inclusion (including a PTSD despite their low TSQ screening score) may also enter the randomization phase. The third group is that of incidental ‘referrals’. Referred participants will not be recruited using the standard screening procedures in cooperating teams. Instead, psychiatrists, psychotherapists, caseworkers or patients from other teams will be offered the opportunity to refer for screening and possible entry in the intervention study. They may do so, if thereare indications the patient may have psychosis and PTSD and may benefit from participation. The diagnostic data of referred participants will be excluded from some of the study’s analyses, but these will be part of all treatment outcome analyses.

### Randomization

All patients meeting the inclusion criteria are asked for written informed consent to participate in the intervention study. Consenting participants receive the pre-treatment (T0) measurements. (Note that for patients with auditory hallucinations six days of T0 measurements on auditory verbal hallucinations are added, using ESM; see Instruments). After T0, participants are randomized to PE, EMDR or the waiting list. A group of fifteen random assignments for each participating therapist will be made. These groups are made using the scientific randomization program on the Internet (http://www.randomizer.org) by the independent randomization bureau of the Parnassia Psychiatric Institute. Each block has five assignments for each condition: PE or EMDR or waiting list. Thus, each therapist treats five people with PE and five people with EMDR. After six months, the therapist will offer the five people from the waiting list the therapy of their choice.

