### Power and sample size calculation

An F-test over three groups with a medium effect-size of treatment compared to waiting list, alpha .05 and power .80 needs 159 participants. Attrition is estimated conservatively to be high at 33%. The needed number of participants is 240. We will use 3 x 80 participants.

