### Analyses

The primary outcome on the PTSD measures will be analyzed using Linear Mixed Models (LMM) with the baseline value as a covariate. LMM will also be used with the secondary outcome measures. Sensitivity and specificity of the screener will be calculated with Receiver Operating Characteristic curves. The predictors will be assessed with (logistic) regression analysis. The moderator and mediator analyses will be calculated with 5,000 bootstraps [124]. The association between working memory and the outcome of therapy is performed by analysis of covariance (ANCOVA’s) and multiple regression analysis. The ESM data will be analyzed by multilevel linear regression modeling using STATA. In case of an effective treatment a cost-effectiveness analysis will be performed. The incremental cost-effectiveness ratios (ICERs) are considered to be a single-point estimate of an underlying continuum. Acceptability curves are produced with bootstrap simulations and confidence intervals. The outcome will be costs in Euro’s per QALY and the costs in Euro’s per day without PTSD gained. If no intervention is effective, which is not expected, a cost-minimization calculation will be done.

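### Allocation is blocked within therapist and only the PE and EMDR arms are therapist-delivered before T6, but the primary mixed model names no term except the baseline value

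*Protocol article*

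**What the plan says.** Three sections of the protocol article bear on this.

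- **Randomization.** "A group of fifteen random assignments for each participating therapist will be made". "Each block has five assignments for each condition: PE or EMDR or waiting list". It follows that "each therapist treats five people with PE and five people with EMDR". The remaining five wait: "After six months, the therapist will offer the five people from the waiting list the therapy of their choice".
- **Analyses.** "The primary outcome on the PTSD measures will be analyzed using Linear Mixed Models (LMM) with the baseline value as a covariate". For the other scales: "LMM will also be used with the secondary outcome measures". No therapist, block or site term is named, and no random-effects structure is given.
- **Power and sample size calculation.** The stated basis is this: "An F-test over three groups with a medium effect-size of treatment compared to waiting list, alpha .05 and power .80 needs 159 participants". The total is then raised to 240 for 33% attrition. No ICC or design effect appears.

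The primary objective sets PE against waiting list and EMDR against waiting list.

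**The concern.** Therapist plays two roles in this design.

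First, it is the randomisation stratum. Differences between therapists' caseloads that are common to all three arms are balanced by design, but a model without the stratum leaves them in the residual. The standard error is then too large and the precision gained by blocking is not used.

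Second, therapist is a source of clustering, but only in the treated arms. Up to T6 the waiting-list participants have received no trial therapy from the therapist. If some therapists obtain better results than others, outcomes within a therapist's PE or EMDR caseload are correlated, while the waiting list has no matching correlation. Both primary contrasts compare a clustered arm with an unclustered one. A model without a therapist term then gives a standard error that is too small.

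The protocol treats such differences as plausible. Its quaternary objectives say therapists' cognitions about treatment may affect outcome, and the therapist attitude questionnaire is to be studied as a predictor of outcome. At stake are the p-values and confidence intervals of both primary contrasts.

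**Working it through.** **The plan's own figure.** A one-way ANOVA with three groups, Cohen's f = 0.25 (assumed for a medium effect, since no value is given) and alpha 0.05 has power 0.805 at N = 159 and 0.797 at N = 156. So 159 reproduces. With 33% attrition, 159/0.67 = 237.3, or 238 rounded up; the plan uses 240.

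**Inputs**
- 5 participants per therapist per arm (Randomization).
- 80 randomised per arm, and 159/3 = 53 completers per arm (Power and sample size calculation).
- 240/15 = 16 therapists, if all blocks fill. This is derived; the article does not state it.
- ICC r: not given, so 0.05 and 0.10 are assumed. Outcome variance is set to 1 in each arm.

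For an arm-versus-waiting-list contrast with n per arm, a model without a therapist term reports a variance of about 2/n. Type I error is 2 × [1 − Φ(1.96 × reported SE / true SE)].

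**A. Therapist differences shared by all arms.** They cancel in the contrast, so the true variance is 2(1 − r)/n and true/reported SE = √(1 − r).

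| r | true/reported SE | type I error |
|---|---|---|
| 0.05 | 0.975 | 4.4% |
| 0.10 | 0.949 | 3.9% |

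**B. Therapist differences in the treated arms only.** With m participants per therapist in the active arm, the true variance is [1 + (m − 1)r]/n + 1/n. For 80 per arm, m = 5. For 53 per arm, m = 53/16 = 3.31. Power is at d = 0.5 for a test using the correct SE: Φ(0.5/SE − 1.96).

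| n per arm | r | active-arm design effect | true/reported SE | type I error | power |
|---|---|---|---|---|---|
| 80 | 0 | 1.00 | 1.000 | 5.0% | 89% |
| 80 | 0.05 | 1.20 | 1.049 | 6.2% | 85% |
| 80 | 0.10 | 1.40 | 1.095 | 7.4% | 82% |
| 53 | 0 | 1.00 | 1.000 | 5.0% | 73% |
| 53 | 0.05 | 1.12 | 1.029 | 5.7% | 71% |
| 53 | 0.10 | 1.23 | 1.056 | 6.4% | 68% |

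**Simulation.** A baseline-adjusted single-visit model without a therapist term was run 4,000 times at 80 per arm. Type I error was 4.9% with no therapist variance; 4.6% and 3.8% under A; and 6.0% and 7.4% under B (r = 0.05 and 0.10 in each case).

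**Both at once.** With each component at 0.05 and 80 per arm, the true variance is (2 − 2 × 0.05 + 4 × 0.05)/80 = 2.10/80, against 2.00/80 reported. The SE ratio is √1.05 = 1.025 and type I error is about 5.6%, between A and B.

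**Would therapist as a fixed stratum suffice?** Not under B. The therapist term removes variance from the residual without modelling the treated-arm variance.
- Residual df are 240 − 16 − 2 = 222.
- Each therapist contributes 15 × (2/3) × (1/3) = 3.33 to the within-therapist sum of squares per unit of squared deviation. Over 15 df that is 50r.
- The residual variance is therefore about 1 − 2r/3 + 50r/222 = 1 − 0.44r.
- The true contrast variance is still (2 + 4r)/80, so the ratio of variances is (1 + 2r)/(1 − 0.44r): 1.125 at r = 0.05 and 1.255 at r = 0.10.
- Type I error is about 6.5% and 8.0%, slightly worse than the 6.2% and 7.4% without any therapist term.

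**The case against.** The strongest reply is that the article gives the primary model a single sentence. That sentence also names no arm, visit or participant effect, all of which a mixed model for this design would need, so it is a summary and not a complete list of terms. A therapist term may well stand in the full protocol or analysis plan. This stands. A reader might infer that the plan excludes therapist from the model; the text does not say so.

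Next, no ICC is given. At ICC zero nothing changes, and at 0.01 type I error stays between 4.9% and 5.2%. The Fidelity checks section describes training in both protocols, supervisor approval of case conceptualizations, monthly supervision and fidelity rating, all of which should narrow therapist differences. The baseline covariate may also absorb part of any shared difference. This stands too, and limits the likely size.

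Finally, the direction is not fixed. Blocking, and having each therapist deliver both therapies, make an unadjusted analysis conservative if taken alone. Only variance confined to treated patients inflates the error rate, and the two partly cancel. A reader might infer that the trial has an inflated false-positive rate; the documents do not establish that.

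What the reply does not remove is that nothing in the article links the therapist-blocked allocation to the analysis. The one adjustment it names is the baseline value, and the sample size calculation allows for no clustering.

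**Conclusion.** The point holds as a conditional one, and the plan should be amended. If the primary model is fitted with the baseline value as its only adjustment, and if therapists differ, the standard errors of both primary contrasts will be off. In case A they are overstated by about 3% to 5% (1/0.975 and 1/0.949). In case B the true SE exceeds the reported one by 5% to 10% with 80 per arm, or 3% to 6% with 53 completers. The sizes rest on an assumed ICC of 0.05 to 0.10, on 16 full blocks, and on a single-visit approximation to the mixed model.

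The effect is moderate. It does not show that the standard errors are wrong as planned, since that needs both an omitted term and non-zero therapist variance, and the article shows neither. Nor does it show that the sample size is wrong: 159 reproduces for the test described, and the power losses in case B depend on the assumed ICC.

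**What to change.** Add to the Analyses section: the mixed model for CAPS and the secondary scales includes therapist (the randomisation block) as a random intercept, plus a therapist random effect in the active arms only, set to zero in the waiting list before T6, with small-sample degrees of freedom such as Kenward-Roger.

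State the fallback as well, because with about 16 therapists the active-arm variance may not be estimable. The fallback must still allow for that variance, for example contrasts computed per therapist and then analysed across therapists, or cluster-robust standard errors by therapist with a small-sample correction. Therapist as a fixed stratum deals with the blocking only and should not be offered as the remedy for clustering in the treated arms.

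The cost is a sentence or two and no new data: assignment lists are drawn per therapist, so the identifier exists for every participant, including the waiting list. Intervals will be slightly wider if therapists differ. The article reports that recruitment is still under way, so the choice can be fixed before outcomes are analysed.
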